**Figure 6 figure6:**
[figure not shown]
Multiple mediation model with independent variable (X), dependent variable (Y), and 2 mediators (Z). Direct effect (c’) and indirect effects (through a x b) are shown.

##### Effect Predictors

###### Overview

Two complementing approaches for analyzing the effect predictors are addressed in steps 8 and 9 of this analysis plan. The specific hypotheses on the effect predictors for both interventions in this particular study are shown in Textbox 3. 

Hypotheses on effect predictors.We expect that for AAF, low perceived physical activity predicts reduction of fatigue severity.We expect that for eMBCT, low perceived concentration, previous experience with mediation exercises, high perceived life threat from cancer, and a high education level predict reduction of fatigue severity.In general, we expect that low perceived social support, longer time since last treatment, suffering from more comorbidities [108], and having strong somatic attributions [57] predict small effects on fatigue severity in both interventions. We expect that high sense of control and good sleep quality predict large effects in both experimental conditions.Other factors will be included for explorative research.

###### Step 8

To find out which participants benefit most from each intervention, the final model of fatigue severity of Step 1 will be extended with potential effect predictors (Textbox 3) that load on the latent growth factors “linear slope” (the “post randomization” linear slope in case of the piecewise model) and, if applicable, “quadratic slope.” As the regression coefficients of all potential effect predictors on the development of fatigue severity will be freely estimated across the 3 intervention groups, this is also called a moderation effect of intervention.

Factor loadings of all hypothesized effect predictors will be reported. Those with the highest loadings will be compared between the conditions in order to find differential effect predictors.

###### Step 9

To identify common effect predictors of homogeneous subpopulations within the heterogeneous population, rather than identifying effect predictors for individual growth patterns, the final step will consist of regressing predictors on latent classes. Therefore, the final model of Step 5, the GMM, will be extended. Again, several potential effect predictors will be regressed onto this model, but this time on the latent class factor, instead of on the latent growth factors. The 3-step procedure proposed by Vermunt [109] will be used for model selection. This step will be carried out separately for each experimental condition.

Factor loadings of all hypothesized effect predictors will be reported. Those with the highest loadings will be compared between the conditions in order to find differential effect predictors.

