#### Core Analysis

##### Effectiveness

###### Overview

Five steps will be taken to evaluate the effectiveness of both interventions, which are explained here in a generic way. The specific hypotheses on the effectiveness of the interventions in our study are shown in Textbox 1.

Hypotheses on effectiveness.
*Primary outcome*
In both experimental conditions:Fatigue severitydecreases during the intervention, andremains decreased after 6 months.After 6 months, fatigue severity has decreased significantly more compared to the control condition.After 6 months, more participants show a clinically relevant reduction of fatigue severity compared to the control condition. A patient is considered clinically improved if he or she has a reliable change index of more than 1.96, according to the reliable change index, and the end score has to be within the normal range, that is a score < 1 standard deviation above the mean of a normative group [94] (ie, a score < 30.4 on the CIS fatigue severity subscale [51]).
*Secondary outcomes*
For both interventions we expect that:After 6 months, mental health and work ability have improved more than in the control condition.After 12 months, fatigue severity, work ability, and mental health remain improved in both intervention groups.Improvements in mental health and work ability after 6 and 12 months are related to reductions in fatigue severity.Return to work and reduced absenteeism will be studied as explorative outcomes.

###### Step 1

Overall effectiveness will be tested in an intention-to-treat analysis by a multiple group latent growth model [79] using data from the first semester. This technique allows individuals to have an individual growth trajectory over time and compensates for missing data in an elegant way.

Since different growth patterns are expected for the pre-intervention period, the intervention period, and the post-intervention period, we will apply piecewise growth modeling so that a slope factor will be estimated for each of the 3 periods (Figure 4). Initial intercepts will be configured to represent the T0b score. This intercept and the pre-intervention slope factor will be constrained to be equal between all 3 conditions (and this assumption will be checked), whereas the subsequent slope factors will be estimated separately for the 3 conditions.

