**Figure 4 figure4:**
[figure not shown]
Simplified representation of a piecewise linear latent growth model, with latent intercept factor (I), latent slope factors preintervention (S(pre)), during the intervention (S(int)), and postintervention (S(post)), and 7 indicators Y. Error terms, correlation coefficients, and covariances are left out.

**Table 5 table5:** Growth factor estimates of 4 different latent growth models.

	Fixed loadings	Time-varying loadings
Piecewise, linear	Mean: I, S(pre), S(int), S(post) Variance: I, S(pre), S(int), S(post)	Mean: I, S(pre), S(int), S(post) Variance: I, S(pre), S(int), S(post)
Quadratic	Mean: I, S, Q Variance: I, S, Q	Mean: I, S, Q Variance: I, S, Q

###### Step 2

The effect size of both experimental interventions will be calculated according to recommendations in Feingold (2009) [95] for both primary and secondary outcomes.

###### Step 3

The proportion of participants who make clinically relevant progress on the primary outcome will be calculated for all 3 conditions; again, in an intention-to-treat analysis. Percentages and standard deviations of the reliable change index will be presented.

###### Step 4

A latent growth model will be built of the primary outcome, in which the outcome measures that have been measured at T3 will also be included, as distal outcomes of changes in the primary outcome during the first semester.

###### Step 5

A growth mixture model (GMM) will be used to further explore differences between individuals, and more specifically to identify subpopulations (latent classes) with homogeneous growth trajectories of the primary outcome within the experimental groups. The Bayesian information criterion will be used for model selection [96].

If convergence considerations allow, this model will be adjusted to allow covariance of the growth factors in order to acknowledge individual variation around the estimated growth trajectories. The trace plots will be inspected to check whether the models have converged to global solutions and a set of diverse starting values will be used. For more information on these analyses, we refer to an introduction to GMM and latent class growth analysis by Jung and Wickrama [97] and examples of similar analyses in the field of Internet interventions [98] and cancer patients [41].

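### Step 8 attaches effect predictors to one post-randomization slope, but the piecewise model has two, and choosing predictors by highest loading does not rank them by 6-month benefit

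*Protocol article*

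**What the plan says.** In the protocol article, Step 1 of the analysis plan describes the piecewise model: "we will apply piecewise growth modeling so that a slope factor will be estimated for each of the 3 periods". The intercept and pre-intervention slope are held equal across arms, "whereas the subsequent slope factors will be estimated separately for the 3 conditions". The Figure 4 caption names the factors: "latent slope factors preintervention (S(pre)), during the intervention (S(int)), and postintervention (S(post)), and 7 indicators Y". Table 5 lists the same set. According to the Randomization section, allocation follows T0b, so S(int) and S(post) both describe the course after randomization.

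Step 8 states its purpose as follows: "To find out which participants benefit most from each intervention, the final model of fatigue severity of Step 1 will be extended". It puts the predictors on the linear slope and, where applicable, the quadratic slope. For the piecewise case it specifies one slope, labelled post randomization: "linear slope in case of the piecewise model". Loadings of all hypothesized predictors are to be reported. A second rule then selects among them: "Those with the highest loadings will be compared between the conditions in order to find differential effect predictors".

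**The concern.** Step 8 extends the Step 1 model but points to a factor which that model does not contain. Two factors fit the label, and the wording is singular. The article does not say whether S(int), S(post), both, or one slope over the whole period is meant.

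The main between-arm hypothesis on fatigue concerns 6 months, and Step 7 uses the T2-T0b difference. That change depends on both slopes. A predictor attached to only one of them has part of its effect left out or forced into the wrong period, so the answer to who benefits most would depend on a choice made later.

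The selection rule adds a second problem. A loading on one growth factor is an effect on that factor, not on benefit at 6 months. Loadings on different factors refer to different time spans and can offset each other. This holds for the quadratic model as well as the piecewise one.

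**Working it through.** The plan gives no figure to reproduce here, so the check compares the model with its use in Step 8 and then illustrates the size.

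**Inputs from the article.** The intervention lasts 9 weeks, T1 falls 2 weeks later, and T2 is at 6 months (Design). CIS fatigue severity is measured at T0b, M3, M6, M9, T1 and T2 after T0a (Fatigue section).

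**Assumptions not in the article.**
- 6 months is 26 weeks, and visits fall at weeks 0, 3, 6, 9, 11 and 26.
- The knot is at week 9 or week 11; the text does not state it.
- There are two variance sets. Set A has SDs of 5 (intercept), 0.3 per week (S(int)), 0.15 per week (S(post)) and 4 (residual). Set B has 6, 0.5, 0.3 and 5.
- Growth factors are uncorrelated, and the predictor is unrelated to the intercept.
- The predictor effect is 3 CIS points.

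**Share of the course.** S(post) covers (26 - 9)/26 = 65% of T0b to T2 with the knot at week 9, and (26 - 11)/26 = 58% with the knot at week 11.

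**Effect of the choice of slope.** For knot k, let t1 = min(t, k) and t2 = max(t - k, 0). The true predictor effect is m(t) = b_int × t1 + b_post × t2. If the predictor is allowed only on the columns X, the expected generalized least squares coefficient is b = (X'V⁻¹X)⁻¹X'V⁻¹m, where V is the model covariance matrix. Three true profiles were used, written as (end of intervention, T2): gain lost (-3, 0), late effect only (0, -3) and gain held (-3, -3). The implied effects at T2, over both knots and both variance sets, are:

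| Predictor attached to | Gain lost (true 0) | Late effect only (true -3) | Gain held (true -3) |
|---|---|---|---|
| S(int) only | -1.9 to -2.3 | -0.7 to -1.1 | -3.0 |
| S(post) only | +1.9 to +2.2 | -3.0 | -0.8 to -1.1 |
| One slope, weeks 0-26 | +0.4 to +0.6 | -3.1 to -3.3 | -2.65 to -2.76 |
| Both slopes | 0.0 | -3.0 | -3.0 |

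With S(int) alone, the late effect keeps 0.69/3 = 23% to 1.07/3 = 36% of its size. With S(post) alone, the held gain keeps 0.81/3 = 27% to 1.14/3 = 38%.

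**Effect of ranking by loading.** The coefficients below are invented for illustration, in CIS points per week (per week squared for b_Q).
- *Different spans.* A loading of -0.20 on S(int) is worth 9 × (-0.20) = -1.8 points at T2 with the knot at week 9. A loading of -0.10 on S(post) is worth 17 × (-0.10) = -1.7. One loading is twice the other, yet the 6-month effects are nearly equal. With the knot at week 11 they are 11 × (-0.20) = -2.2 and 15 × (-0.10) = -1.5.
- *Cancellation, piecewise.* Loadings of -0.20 on S(int) and +0.106 on S(post) give -1.8 at week 9 and -1.8 + 17 × 0.106 ≈ 0 at T2. The second value was chosen to cancel.
- *Cancellation, quadratic.* Loadings of b_S = -0.26 and b_Q = +0.01 give 26 × (-0.26) + 676 × 0.01 = -6.76 + 6.76 = 0 at T2.

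**The case against.** The strongest reply is that the label may only be meant to separate the later slopes from S(pre), which is held equal across arms. On that reading both later slopes carry predictors, as the plural in Step 1 suggests, and the first distortion disappears. This reading is possible, but the wording is singular and the article does not settle it.

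A reader might go further and infer that the plan will report predictors of lost early gains and miss predictors of maintenance. The document does not support that. It would require S(int) alone to be meant. Under S(post) alone the pattern reverses, and even under S(int) alone a late effect is attenuated rather than wholly lost. Loadings of all hypothesized predictors are reported in any case; the highest-loadings rule governs only which ones are compared between conditions. Nor can it be said that the quadratic model would rank on the linear slope alone, since Step 8 puts predictors on the quadratic factor too.

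The ambiguity over the slope arises only if the piecewise model is preferred to the quadratic one. Step 9 offers a second route through latent trajectory classes that needs no single slope. It is not a replacement, because the classes are formed within the experimental groups and the step runs separately for each experimental condition. It therefore cannot compare predictors with control.

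Finally, a fall in fatigue during the intervention is itself a primary-outcome hypothesis, so a predictor of S(int) is a legitimate result even if the gain later fades. That stands, and it is a reason to report both coefficients and not only the 6-month effect.

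**Conclusion.** The point holds in a limited form. Step 8 names a target that is not a factor of the piecewise model, while two slopes fit its description. Using either one alone distorts predictor effects on 6-month benefit, in opposite directions. In the illustration, an effect that is truly 0 appears as about 2 points either way, and a real 3-point effect shrinks to roughly a quarter to a little over a third. These sizes rest on the assumed visit weeks, knot and variances, and would change if the growth factors were allowed to covary. They are not figures from the article. If both slopes are meant, this part reduces to a wording correction.

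The selection rule is a separate weakness that remains under both the piecewise and the quadratic model. Loadings on separate growth factors do not order predictors by benefit at 6 months.

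The matter touches the third, exploratory objective and leaves the primary effectiveness test alone. It is still worth correcting, because the article presents its methods as fixed in advance and Step 8 is the only predictor analysis that spans all three arms.

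**What to change.** Amend Step 8 in two places.

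1. If the piecewise model is final, state that both S(int) and S(post) are regressed on each predictor in each arm, and that both coefficients are reported.
2. In either model, also report the model-implied predictor effect on T0b-to-T2 change with a 95% interval, and use it in place of the highest loading to select predictors for comparison between conditions. With k the model's actual knot in weeks and T2 at week 26, the effect is k × b_int + (26 - k) × b_post for the piecewise model and 26 × b_S + 676 × b_Q for the quadratic one. The model's own time scores should replace these weights where they differ.

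This needs a sentence or two and a derived parameter in the same model, with no new data. Compared with attaching predictors to one slope, the cost is one more coefficient per predictor and arm, with somewhat less precision for each.

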#### Randomization

If the eligibility-criteria are met, the researcher confirms the participant’s enrollment. Subsequently, the activity sensor is given to the participant and its setup is explained in a face-to-face meeting in the participant’s home or another mutually convenient location. The second baseline assessment starts (T0b), followed by randomization of the participant to 1 of the 3 conditions by a script embedded in the researchers’ Web portal and uses the random function of php (rand(1,3)) [50]. The researchers can neither influence nor predict the outcome of the randomization process. Subsequently, the researcher emails the participant about the outcome of randomization, requests the participant to complete the third baseline assessment (T0c), and assigns the participant to a therapist in case the participant has been randomized to an experimental condition. Participants who do not fill out T0c are considered as not being included. The allocation of a therapist is based on current availability of the therapists who are involved in the trial.

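### Step 9 can report correlates of entry fatigue as effect predictors, because Steps 5 and 9 do not keep pre-randomization fatigue out of the latent classes

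*Protocol article*

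**What the plan says.** All references are to the protocol article.

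- **Step 1 (Effectiveness)** defines the growth model of CIS fatigue severity. The model is piecewise, "so that a slope factor will be estimated for each of the 3 periods", and it is compared with a quadratic model that has an intercept, one slope and one quadratic factor. On the intercept: "Initial intercepts will be configured to represent the T0b score". On constraints: "This intercept and the pre-intervention slope factor will be constrained to be equal between all 3 conditions".
- **Randomization** places T0b before allocation: "The second baseline assessment starts (T0b), followed by randomization of the participant to 1 of the 3 conditions".
- **Step 5** uses a growth mixture model "to identify subpopulations (latent classes) with homogeneous growth trajectories of the primary outcome within the experimental groups". It does not list which growth factors may differ between classes. On variation inside a class: "If convergence considerations allow, this model will be adjusted to allow covariance of the growth factors".
- **Step 8** lets the predictors act on the slope factors, and in the piecewise case on the slope after randomization. Coefficients are free across the three conditions.
- **Step 9** extends the final Step 5 model, and "several potential effect predictors will be regressed onto this model, but this time on the latent class factor". It is run separately in each experimental condition. All loadings are reported, and the highest are compared between conditions to find differential effect predictors.

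**The concern.** An effect predictor should say who changes more after allocation. Step 8 respects this by pointing the predictors at change. Step 9 replaces that target with class membership, which can mix entry severity with change. Two classes may differ mainly in how fatigued patients were at T0b. A candidate that marks only that difference would then appear under the label of effect predictor.

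Several Textbox 3 candidates, such as sleep quality, sense of control, comorbidity and social support, are plausibly related to entry fatigue. The Discussion wants knowledge of differentiating factors to guide which patients go to which intervention, so a mislabelled severity marker could feed into that advice.

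**Working it through.** **1. What the classes can contain.** If the piecewise model is carried into Step 5, the mean path of class k is

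I_k + S(pre)_k × pre + S(int)_k × int + S(post)_k × post.

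I is fatigue at T0b and S(pre) covers the time before it, so both precede allocation. The only stated equality constraint on them is across the three conditions, not across classes. In the quadratic form (I, S, Q) the intercept is still at T0b, but there is no separate pre-intervention slope. The S(pre) part of the point therefore holds only for the piecewise model.

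**2. Why within-class variance matters.** If patients in a class share one path apart from residual error, lasting differences in level between patients can be absorbed only by splitting them into classes. If a class has its own spread of intercepts, level differences can sit inside the class. Step 5 makes the growth-factor covariance conditional on convergence, so the restricted version is a possible final model.

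**3. Size, by simulation.** The plan states no figure to reproduce. A predictor was generated that correlates r with true baseline level and is unrelated to change.

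Inputs from the article:
- patients per experimental arm: 330/3 × 0.70 = 77, as stated under Power Analyses (control: 110 × 0.85 = 93.5, stated as 94);
- entry score of at least 35, and scale range 8-56;
- seven first-semester assessments (T0a, T0b, M3, M6, M9, T1, T2);
- number of classes chosen by BIC.

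Assumed inputs:
- baseline mean 42 and SD 6, residual SD 4.5, T0a four weeks before T0b;
- weekly change during the intervention either continuous (mean -0.6, SD 0.5) or in two groups (40% at -1.3, 60% at -0.15);
- one to three classes, with an F-test of the predictor across modal classes at .05 as a stand-in for the three-step procedure.

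Share of runs in which the baseline-only predictor was flagged:

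| Class model | r=0 (300 runs) | r=.3 (60 runs) | r=.5 (300 runs) |
|---|---|---|---|
| No within-class variance | 3-5% | 30-33% | 73-76% |
| Intercept variance within class, all means free | 3% | 5-10% | 14-27% |
| As above, with I and S(pre) means equal across classes | 2-5% | 5-7% | 8-17% |

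The Monte Carlo standard error is √(p(1-p)/runs). For example, √(.27 × .73/300) = 2.6 points and √(.30 × .70/60) = 5.9 points. The r=0 column shows that the excess is not a fault of the test. With no variation in change at all (60 runs), the model without within-class variance still flagged the predictor in 37% (r=.3) and 82% (r=.5). With intercept variance, BIC then chose one class in 59 or 60 of 60 runs and almost nothing was flagged (0-2%).

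**4. Other assumed values.**
- Baseline SD 7, residual SD 4, up to four classes, 100 runs per cell: 32-39% (r=.3) and 60-63% (r=.4) without within-class variance, 6-14% with intercept variance, and 3-7% with equal pre-randomization means.
- A further run with 77 per arm and up to three classes: 24-31% (r=.3) and 67-74% (r=.5) without within-class variance, 9-19% with intercept variance, and 8-15% with equal intercept means. Adjusting the class regression for T0a/T0b fatigue gave 3-9%.

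**5. Pooled range.** Without within-class variance the rates span 24-39% at r=.3 and 67-82% at r=.5. With intercept variance, and wherever change truly varies, they span 5-27%.

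**The case against.** A reader might infer that the plan forms its classes on the whole trajectory, pre-randomization level and slope included, and so will list severity markers as effect predictors. The article does not say this. Step 5 speaks of growth trajectories and is silent on which factors are class-specific. The intercept and constraint text belongs to Step 1. The article describes its plan as general, and a fuller document may settle the matter. This stands: the plan can produce the error, but it does not prescribe it.

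The large rates belong to the restricted model. Step 5 intends to add covariance where it can, and its wording does not strictly say that the starting model has no growth-factor variance. With intercept variance the risk is modest, and at r=.3 it is hard to tell apart from the rate with equal means. This also stands. The fallback is not remote, though: arms planned at 77 are small for a mixture model, and the January 2015 sizes were 36 and 24, with 19 patients not yet randomized.

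Step 9 states no significance filter; it reports every loading and compares the highest. The rejection rates therefore show how strongly class can carry baseline level, not how many factors will be named. In addition, a pure severity marker has the same expected relation to baseline in both randomized arms, so it should tend to look common and not differential. That softens the allocation worry. It does not remove the mislabelling of common predictors.

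Finally, Step 8 tests the same hypotheses on change across three arms, and Step 5 is exploratory. This lowers the weight of the point. It does not justify the label in Step 9, which is a stated choice and not a detail left to another document.

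**Conclusion.** The point holds in a limited form. Steps 5 and 9 leave pre-randomization level (and S(pre), if the piecewise model is used) free to separate the classes, while predictors of class are called effect predictors. A factor related only to entry severity can therefore be reported as one. Under assumed values the risk is large without within-class variance (about 25-40% at r=.3 and 65-80% at r=.5) and modest with intercept variance within class (about 5-27%). These sizes rest on the assumed means, SDs, correlations and timing, and on a modal-class test in place of the three-step procedure. Because Step 9 uses no control arm, its predictors would remain prognostic within an arm even if baseline level were fully removed. Only Step 8 addresses moderation by intervention.

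**What to change.** 1. In Step 9, include baseline CIS fatigue (T0a/T0b) as a covariate when the candidates are regressed on class. In the simulation that tried this, 3-9% were flagged. The data are already collected; the cost is a few more parameters in a small arm.
2. In Step 5, allow patient-level intercept variance within class. If that model does not converge, say so next to the Step 9 results.
3. Report Step 9 results as predictors of fatigue course within an arm, and leave claims about effect predictors to Step 8. This is a change of wording only.
4. As a sensitivity analysis, show classes with I (and S(pre), if used) held equal across classes. This should not be the main model: the constraint is misspecified if response classes truly differ in entry severity, and it still left up to 17% flagged at r=.5.

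### Step 9 compares predictor loadings on latent class between the two experimental arms without first requiring that the classes mean the same in both arms

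*Protocol article*

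**What the plan says.** Step 5 (Core Analysis, Effectiveness) introduces a growth mixture model (GMM) of fatigue severity "to identify subpopulations (latent classes) with homogeneous growth trajectories of the primary outcome within the experimental groups". On the choice of model it says: "The Bayesian information criterion will be used for model selection". It does not say whether one model covers both experimental arms or each arm has its own.

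Step 9 (Effect Predictors) builds on this: "Therefore, the final model of Step 5, the GMM, will be extended". Predictors are regressed "but this time on the latent class factor, instead of on the latent growth factors". It continues: "The 3-step procedure proposed by Vermunt [109] will be used for model selection", followed directly by "This step will be carried out separately for each experimental condition".

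Step 9 then closes with a sentence that also closes Step 8: "Those with the highest loadings will be compared between the conditions in order to find differential effect predictors".

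Step 8 works differently. It extends the Step 1 growth model, regresses the growth factors on the predictors in one multi-group model, and leaves the coefficients free across all three groups.

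**The concern.** In Step 9 the class is the outcome of the regression. Coefficients from two arms can be set against each other only if that outcome is defined the same way in both. Classes estimated arm by arm need not agree in number, shape or meaning. The improving class might be one of two in AAF and one of three in eMBCT, with a different average fall in fatigue. A gap in loadings would then mix a real difference in who benefits with a difference in who is counted as an improver.

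The Background and the Discussion both say that differentiating predictors should help direct patients to the more suitable intervention. An artefact of class definition could be read as evidence of who suits which therapy.

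**Working it through.** The plan gives no figure for this comparison, so there is none to reproduce. The check has a textual part and two illustrations. All mixture inputs in the illustrations are assumed and do not come from the article.

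**1. The text side by side**

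| Question | Step 5 | Step 9 | Step 8 |
|---|---|---|---|
| Outcome of the predictor regression | none (classes are formed here) | latent class | growth factors |
| Unit of fitting | within the experimental groups; pooled or per arm not stated | each experimental arm separately | one multi-group model, three arms |
| Common definition across arms | not stated | not stated | same growth factors in one model |
| Loadings compared between arms | no | yes | yes |

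For arm *g*, write logit P(C_g = improver | x) = a_g + b_g·x, where C_g is the class defined by the model fitted for that arm. The difference b_AAF − b_eMBCT is a difference in predictor effect only if C_AAF and C_eMBCT are defined alike. Step 9 neither imposes nor tests this.

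**2. Can class structure alone produce a differential predictor?**

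Assume the predictor lowers 6-month fatigue by 2 points per SD in both arms, with residual SD 3. Arm A is a mixture of mean changes −2 and −16 (50% each). Arm B is a mixture of 0, −10 and −22 (30%, 40%, 30%). Fit an equal-variance normal mixture to the change scores in each arm, choose the number of classes by BIC, and also force two classes. Then regress most-likely membership of the improving class on the predictor.

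| n per arm | Arm | Linear slope | Classes by BIC | Log-odds ratio, two classes forced |
|---|---|---|---|---|
| 20,000 | A | −1.93 | 2 | 0.13 |
| 20,000 | B | −1.96 | 3 | 0.27 |
| 77 (150 runs) | A | −1.99 | 2 in 149 runs, 3 in 1 | 0.14 (SD 0.24) |
| 77 (150 runs) | B | −2.12 | 1, 2, 3 in 73, 35, 42 runs | 0.36 (SD 0.29) |

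At n = 20,000 the linear slopes agree to 0.03, yet the log-odds ratio in B is about double that in A (0.27/0.13 ≈ 2.1). So the mechanism is real. At n = 77 the mean gap is 0.36 − 0.14 = 0.22. The sampling SD of a difference is √(0.24² + 0.29²) ≈ 0.38, so in a single trial the artefact would be smaller than the noise.

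**3. Can identical arms receive different class numbers?**

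The planned size is 330/3 = 110 per arm, and 110 × 0.70 = 77 at T2, as the Power Analyses section states. Assume both arms come from the same population: 40% fall by 10 (or 14) points and 60% by 1.5, with 6 time points, intercept SD 4 and error SD 5. Fit 1 to 4 classes in each arm, choose by BIC, and count the pairs with unequal class numbers. Runs differed in details such as the time shape of the class means, so ranges are given.

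| Fitted model | 10-point fall | 14-point fall |
|---|---|---|
| No within-class covariance | 26–56% across both falls | (same range) |
| Random intercept within class | 20–60% | 2–8% |

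With a random intercept, a 10-point fall and 110 per arm, one run gave 22%. Unequal number is only one form of mismatch; classes equal in number can still differ in shape.

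**The case against.** **Separate classes are not stated.** A reader might infer that the plan explicitly derives the classes separately in each arm. It does not. Classes are formed in Step 5, and both steps speak of a single GMM. A three-step procedure takes classes from an earlier model and relates predictors to them afterwards, so one pooled class solution with arm-specific regressions fits the text. On that reading the class is the same outcome in both arms and the objection falls away. This stands as a possible reading. The per-arm reading is still more natural, because the step that is repeated in each arm includes extending the GMM and selecting the model.

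**Matching classes can be compared.** A reader might also infer that the Step 9 loadings cannot be interpreted at all. That goes too far. If the arms yield matching classes, the comparison can be read.

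**Step 8 already offers a common scale.** This is true, and it limits the harm. It does not repair Step 9, which draws its own conclusion about differential predictors.

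**The simulated rates depend on the model.** This is also true. A model without within-class covariance cannot represent the assumed intercept spread, so BIC adds classes; in one run it found the true two classes in only 6% of arms (10-point fall) and 0.5% (14-point fall). Step 5 intends to free growth-factor covariance if convergence allows, and with a 14-point fall that nearly removes the problem. The analysis is also by intention to treat, so the usable number is nearer 110 than 77. A headline of about half of trials would therefore not be supported.

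**Much of this is detail for a full analysis plan.** The form of any equality constraint is such detail. The separate fitting and the between-arm comparison, however, are stated in the article.

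**Conclusion.** The point holds in limited form. Step 9 is run per experimental arm and its loadings are then compared across arms, with no requirement that the classes agree. On the natural reading, a stated rule can label a predictor as differential because of how classes were formed. On the pooled reading, the article leaves open a choice that decides whether the comparison is valid.

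The size cannot be given as one number. Under the assumed mixtures, the share of identical arm pairs with unequal class numbers ran from 2% to 60%, driven by class separation and by whether within-class covariance is modelled. The article fixes neither.

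The primary effectiveness analysis is untouched. The point concerns the last step of the plan, built on a model introduced to explore differences between individuals, and a common-scale comparison exists in Step 8. It is minor.

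**What to change.** 1. In Step 5, state that one GMM is fitted to both experimental arms with arm as a known group, with class sizes free. Use BIC to test whether class trajectories can be held equal across arms.
2. If they can, run the three-step regression of Step 9 on the common classes with predictor-by-arm terms. Report those terms with 95% intervals in place of a comparison of the highest loadings.
3. If they cannot, report Step 9 within each arm only, as descriptive, and rest all claims about differential predictors on the Step 8 multi-group model.

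The cost is one extra joint model, and possibly no differential claim from Step 9. Because equality is tested and not imposed, two theoretically different therapies are not forced into the same trajectories. No change to data collection is needed.
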